#### 2.8.1.
*Screening visit*.

Before trial initiation, patients who want to participate in the study would be thoroughly explained about the procedure by the investigators, and the participants would be requested to voluntarily submit the written consent. Then, interview and physical examination would be conducted to assess the eligibility. Collected data are the demographic and sociological information, medical history, treatment history, vital signs (blood pressure, pulse rate, and body temperature), visual acuity tested by [name] vision Test Chart for 3 m, and intraocular pressure measured by a tonometer (HNT-1; Huvitz Co., Ltd., Anyang, Republic of Korea). In accordance with the inclusion and exclusion criteria, suitable participants will receive an identification code, and the eligibility judgement would be recorded on the case report form (CRF). For the selected participants, the next visit date would be designated.

#### 2.8.2.
*Visit 1*.

On visit 1, randomization and initial treatment would be executed. Visit 1 is scheduled within 7 days after the screening visit. Participants who passed screening are allowed to receive examinations and treatment of visit 1 on the same day as the screening visit. During this visit, investigators would assess the changes in medical and medication history of the participants, and record them on the CRF. Visual acuity, visual analog scale (VAS) for subjective symptoms, OSDI, Schirmer I test, and quality of life (QoL) will also be examined. Certain examinations, including vital signs, changes in the medical and medication history, visual acuity, and adverse events (AEs) will be conducted in every visit. Before treatment, the participants would be randomly allocated to the experimental or control group. The therapist would treat the participants with the BMA or the IDA according to the allocation result. At the end of the visit, the clinical research coordinator would schedule the next visit.

#### 2.8.3.
*Visits 2 to 12*.

From visit 2 to 12, investigators would record the changes in regular examinations, including visual acuity, medical and medication history, and AEs, on the CRF since the last visit. The allocated intervention would be continuously performed for the participant during this period. At the end of each visit, the next visit would be scheduled. Midterm assessment for some outcomes would be executed on visit 7. Before treatment during the visit, the VAS for subjective symptoms, the OSDI, and the QoL would be examined.

#### 2.8.4.
*Visit 13*.

Visit 13 is the final follow-up visit, and would be scheduled within 3 days from the time when 4 weeks passed from the visit 1. Investigators would record the changes in the routine examinations since visit 12 on the CRF. The final assessment would be performed for the primary and secondary outcomes, including the OSDI, the VAS for subjective symptoms, the QoL, the Schirmer I test, and general assessment by the participants and investigators. Participants’ compliance for this trial would be also examined during this visit.

#### 2.8.5.
*Extra visits*.

Extra visits can be scheduled if the participants request for them or based on the investigators’ decision considering its necessity. It is allowed only if the AEs persist until the end or suspension of the trial, or if there are demands for extra follow-ups after treatment termination from the investigators or the participants. If permitted, the investigators would carry out follow-ups for the emerged AEs.

### 2.9.
*Outcomes*

#### 2.9.1.
*Primary outcome*.

The primary outcome of this study is OSDI.^[17]^ The OSDI is assessed on visit 1 (prior to intervention), 7, and 13. The OSDI consists of total 12 questions for visual acuity (6 questions), ocular symptoms (3 questions), and provoking environmental factors (3 questions).^[18]^ The severity is scored as none of the time = 0, some of the time = 1, half of the time = 2, most of the time = 3, and all of the time = 4. The total score is calculated according to the following formula.^[19]^

$$\begin{array}{ll} & OSDI\;score\\ & \;\;\;=\frac{(sum\;of\;scores\;for\;all\;questions\;answered)\times 100}{(total\;number\;of\;questions\;answered)\times 4} \end{array}$$

If a respondent does not correspond to a question, the question is not scored and it is treated as “not applicable.” The range of an OSDI score is from 0 to 100, and a higher score indicates more severe symptoms. The values of 0–12, 13–22, 23–32, and 33–100 indicate normal, mild, moderate, and severe dry eye, respectively.^[18,20]^

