## 1. Introduction

Dry eye syndrome is a lacrimal disease caused by insufficient secretion or excessive evaporation of tears, which leads to ocular surface damage, and accompanies irritating symptoms, including discomfort, foreign body sensation, or dryness of the patient’s eye.^[1]^ According to a report from the National Health Insurance Service of Korea in 2018, the prevalence of dry eye has steadily increased by 2.1% annually since the recent 5 years.^[2]^ Nowadays, dry eye can be aggravated by various environmental factors, which include excessive use of visual display terminals, increase in indoor stay, fine dust, or growing use of contact lenses.^[3–5]^ Although artificial tears, corticosteroid eye drops, cyclosporine, therapeutic contact lenses, protective glasses, and punctal occlusion have been suggested as treatments, they have several side effects and are not considered fundamental treatment options.^[6–9]^

In Korean medicine, acupuncture or herbal medication, which clear heat, nourish the yin and body fluid, or supplement the blood and qi, have been traditionally used for dry eye.^[10]^ Clinically, acupuncture has been considered the main Korean medicine treatment for dry eye. Hence, studies^[11–14]^ on the efficacy of acupuncture for dry eye have been steadily reported; however, these prior studies are mainly limited to case reports. Thus, a randomized controlled trial (RCT) is necessary to establish the evidence of acupuncture for dry eye.

Intradermal acupuncture (IDA) is a type of acupuncture commonly used for dry eye in clinical practice; however, related clinical studies are rare. Thus, we conducted preliminary studies on the efficacy and safety of IDA for dry eye. First, we searched RCTs on IDA for dry eye from domestic and foreign databases, and analyzed 4 eligible RCTs.^[15]^ Thereafter, we conducted a preliminary RCT (not published yet) comparing IDA with body acupuncture for dry eye. This study has suggested significant improvement of the ocular surface disease index (OSDI) in both interventions, no difference upon intergroup comparison, and safety of IDA.

This study assesses the efficacy and safety of a biodegradable microneedle acupuncture (BMA) for patients with dry eye compared to conventional IDA. Based on the results, this study aims to demonstrate the superiority of BMA for dry eye compared to conventional IDA.

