##### 2.9.2.1.
*VAS for subjective symptoms*.

The VAS is evaluated by marking the overall severity of discomfort arisen from dry eye during the last week on a 100 mm straight line. The left end (0 mm) indicates “no symptoms,” and the right end (100 mm) indicates “the worst discomfort.” When the participants mark a dot on the VAS line, investigators score it by measuring the length from the left end to the dot. The score ranges from 0 to 100. The measurement is conducted on visits 1, 7, and 13.

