##### 2.9.2.2.
*Quality of life*.

The QoL assesses the life of the participants associated with dry eye symptoms during the last week. It is scored from 0 (the worst) to 6 (the best) by the participants themselves. The following is a question to the participants: “During the last week, how much was the overall quality of your life related to dry eye symptoms?” The assessment is conducted during visits 1, 7, and 13.

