#### 2.10.1.
*Analysis for the primary and secondary outcomes*.

The same analysis method will be used for the primary and secondary outcomes. The measurements from each group would be presented as descriptive statistics, including mean, median, standard deviation, minimum, and maximum. In the intragroup comparisons, the differences in the outcomes following the interventions would be analyzed using the Student’s paired *t* test or the Wilcoxon signed-rank test, and 95% confidence intervals would be presented. The differences between the 2 groups on each visit would be statistically assessed using the 2-sample *t* test or the Mann–Whitney test, depending on whether the normality is satisfied. For missing values, a last observation carried forward method would be used to handle.

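### The primary outcome, OSDI, has no decision visit and is tested between groups at each visit without adjustment, so a superiority claim could rest on visit 7 or visit 13

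*Protocol article*

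**What the plan says.** The Introduction states the aim: "this study aims to demonstrate the superiority of BMA for dry eye compared to conventional IDA". The Discussion returns to it and speaks of superiority as something this study may prove.

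Section 2.9.1 defines the endpoint only by its instrument: "The primary outcome of this study is OSDI". The schedule follows: "The OSDI is assessed on visit 1 (prior to intervention), 7, and 13". The section does not say which visit is primary, or whether the score or its change from visit 1 is compared.

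Section 2.10.1 sets the analysis. "The same analysis method will be used for the primary and secondary outcomes", and "The differences between the 2 groups on each visit would be statistically assessed" with a two-sample t test or a Mann-Whitney test, depending on normality. It singles out no visit and gives no order, adjustment or test level.

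Three other places bear on which visit was intended:
- Section 2.8.3 calls visit 7 a midterm assessment, done before that day's treatment.
- Section 2.8.4 calls visit 13 the final assessment for primary and secondary outcomes.
- Section 2.11.2 treats an OSDI missing at the beginning or end of the trial as a severe violation. It does not list one missing at visit 7.

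**The concern.** A superiority claim needs one comparison that decides it. Here two post-baseline comparisons of the primary outcome stand side by side under the same rule, and they answer different questions. At visit 7 participants have had 6 of 12 sessions; at visit 13 they have had the full course. A group difference at half-course is not the same claim as one at the end of treatment.

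If the deciding visit is not fixed beforehand, it can be chosen once both results are known, and the false-positive rate for the claim rises above that of a single test.

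Read literally, the instruction to test at each visit also covers visit 1, before any treatment. In a randomized trial that test can only detect chance imbalance. It adds nothing to the error rate of the efficacy claim, but it shows that the rule does not separate the visits by purpose.

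**Working it through.** **The plan's own figure.** Section 2.2 takes 12 per group from a pilot rule and allows for 20% dropout: 12 / (1 − 0.20) = 15 per group, 30 in total. This reproduces. It uses no effect size, power or test level, so naming a decision visit does not alter it.

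**Inputs**
- Post-baseline OSDI measurements: 2, at visits 7 and 13 (section 2.9.1).
- Participants per group: 15 planned, 12 after the assumed dropout (section 2.2).
- Test level: not stated. Two-sided 0.05 is assumed, in line with the 95% intervals in section 2.10.1.
- Correlation r between OSDI at visits 7 and 13: not stated. The range 0.3 to 0.9 is assumed.

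**Formula.** With no true difference at either visit, the chance of at least one significant result is 1 − P(|Z₁| < 1.96 and |Z₂| < 1.96), where Z₁ and Z₂ are standard normal with correlation r. For false positives favouring BMA only, it is 1 − P(Z₁ < 1.96 and Z₂ < 1.96). Independent tests give the upper reference: 1 − 0.95² = 0.0975, and in one direction 1 − 0.975² = 0.0494.

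| r | At least one false positive, either direction | Favouring BMA only |
|---|---|---|
| 0.3 | 0.0951 | 0.0476 |
| 0.5 | 0.0907 | 0.0454 |
| 0.7 | 0.0835 | 0.0417 |
| 0.9 | 0.0704 | 0.0352 |
| Single test | 0.05 | 0.025 |

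**Check at the trial's size.** One million simulated trials of paired two-sample t tests with 15 per group (critical value 2.048) gave 0.0951, 0.0911, 0.0839 and 0.0707 at the same four correlations. With 12 per group (critical value 2.074) they gave 0.0958, 0.0912, 0.0842 and 0.0710. Small samples do not change the picture.

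**Keeping both visits decisive.** Bonferroni would set each test at 0.05 / 2 = 0.025. For a two-sample t test with 80% power, the detectable standardized difference would then rise from 1.06 to 1.18 at 15 per group, and from 1.20 to 1.34 at 12 per group. In a trial this small, one decision visit is the cheaper choice.

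**The case against.** The strongest reply is that this is a journal article. The full protocol or an analysis plan may name the decision visit, and section 2.10.1 lists tests to be run without saying that any significant one proves superiority. The midterm and final labels, with the violation rule in section 2.11.2, also make visit 1 to visit 13 the natural contrast. The study is a pilot sized by a rule of thumb, and the Discussion plans a confirmatory trial.

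Part of this stands. The documents do not say that either visit suffices; that follows from following the text as written. The intended visit is probably 13, and the pilot setting limits the consequences. But the point does not rest on silence alone. Section 2.10.1 positively prescribes testing at each visit, so an analysis plan naming one visit would be narrowing what the article fixes. The pilot label also sits beside an explicit aim to demonstrate superiority.

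Two stronger readings are tempting and not supported:
- A reader might infer that every outcome is tested at every visit. VAS and quality of life do share the OSDI schedule ("The measurement is conducted on visits 1, 7, and 13" and "The assessment is conducted during visits 1, 7, and 13"). But Schirmer I has one post-baseline measurement and the general assessment is made only at visit 13.
- A reader might count all 8 post-baseline comparisons as routes to superiority, which would give about 19% to 30% at common correlations of 0.7 to 0.3. Those other outcomes are labelled secondary. Sharing a test method does not give them the standing of the primary outcome, and nothing says a secondary result can establish superiority.

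It is also fair to say that baseline adjustment is not needed to remove the multiplicity. Naming visit 13 alone would do that.

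**Conclusion.** The point holds for the primary outcome. OSDI has no decision visit, its between-group tests are prescribed at each visit without adjustment, and the trial aims to demonstrate superiority. Sections 2.8.3, 2.8.4 and 2.11.2 favour visit 13 without making it decisive.

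The inflation is moderate: about 7.0% to 9.5% against 5% in either direction, or about 3.5% to 4.8% against 2.5% in favour of BMA. This assumes two-sided 5% tests, a correlation of 0.9 to 0.3 between visits 7 and 13, no true difference at either visit, and that a significant result at either one would be taken as superiority. It should be corrected, and the correction is inexpensive.

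**What to change.** In sections 2.9.1 and 2.10.1:
- Define the primary endpoint as the between-group difference in OSDI at visit 13, adjusted for visit 1 OSDI by analysis of covariance. State that this is the only test of superiority, and give its significance level and sidedness.
- Report visit 7 OSDI and all secondary outcomes as supportive estimates with 95% confidence intervals, with no superiority claim.
- Describe visit 1 values by group without a significance test. The covariate then deals with chance imbalance in OSDI, which is likely to matter with 15 per group.

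The change should be dated and made before database lock; the article reports the trial as ongoing.

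The cost is a short amendment. Visit 1 OSDI is already collected and no patients are added. Two things are given up: an isolated visit 7 result could no longer be claimed as superiority, and the primary test changes from a two-sample t or Mann-Whitney test to a baseline-adjusted model, which uses one more degree of freedom (27 instead of 28 residual with 30 participants).

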#### 2.9.2.
*Secondary outcomes*.

##### 2.9.2.1.
*VAS for subjective symptoms*.

The VAS is evaluated by marking the overall severity of discomfort arisen from dry eye during the last week on a 100 mm straight line. The left end (0 mm) indicates “no symptoms,” and the right end (100 mm) indicates “the worst discomfort.” When the participants mark a dot on the VAS line, investigators score it by measuring the length from the left end to the dot. The score ranges from 0 to 100. The measurement is conducted on visits 1, 7, and 13.

##### 2.9.2.2.
*Quality of life*.

The QoL assesses the life of the participants associated with dry eye symptoms during the last week. It is scored from 0 (the worst) to 6 (the best) by the participants themselves. The following is a question to the participants: “During the last week, how much was the overall quality of your life related to dry eye symptoms?” The assessment is conducted during visits 1, 7, and 13.

##### 2.9.2.3.
*Schirmer I test*.

The Schirmer I test is used to measure the tear secretion. Upon folding the tip, the Schirmer strip (BIO Color Tear Test; Bio Optics, Seongnam, Republic of Korea) is inserted to the lateral 1/3 point of the lower eyelid. The folded tip should be in the conjunctival sac. Facing their eyes up, the participants close their eyes for 5 minutes immediately after inserting the strips. After 5 minutes, the investigators measure the length of the strip soaked in tears. The test is conducted during the screening visit and visits 1 and 13.

##### 2.9.2.4.
*General assessment*.

The general assessment in this study indicates a comprehensive assessment for the improvement in dry eye symptoms using a 5-grade Likert scale.^[21]^ It is assessed by the participants themselves or investigators during visit 13, the final visit upon termination of all the treatments. The responses to the questions include excellent, good, fair, poor and aggravation. “Excellent” corresponds to the responses that dry eye and its concomitant symptoms were completely improved, the treatment demonstrated clear therapeutic effect, or daily life activities were obviously improved. “Good” corresponds to the response that dry eye and its concomitant symptoms still remain; however, they have greatly improved compared to before participating in this trial. “Fair” corresponds to the response that dry eye and its concomitant symptoms remain; however, they are slightly improved or tend to improve after the trial. “Same” corresponds to the response that little change is observed comparing before and after the trial. “Aggravation” corresponds to the response that dry eye symptoms are more severe than before participating in this trial.

#### 2.9.3.
*Safety assessment*.

AE includes any unintended results that occurred even though the medical device was appropriately used according to the instructions. The expected AEs of the IDA are local pain from the treated area, local bleeding from the treated area, allergic reactions of the skin, infections, localized infection symptoms (redness, swelling, and/or local pain), nausea, vomiting, headache, and/or dizziness.^[22,23]^ For the BMA, redness on the treated area, skin irritation, and/or skin erosion are also expected in addition to the expected AEs of the IDA. Investigators would check and record the emergence of AEs on the CRF at each visit.

### 2.10.
*Statistical analysis*

#### 2.10.1.
*Analysis for the primary and secondary outcomes*.

The same analysis method will be used for the primary and secondary outcomes. The measurements from each group would be presented as descriptive statistics, including mean, median, standard deviation, minimum, and maximum. In the intragroup comparisons, the differences in the outcomes following the interventions would be analyzed using the Student’s paired *t* test or the Wilcoxon signed-rank test, and 95% confidence intervals would be presented. The differences between the 2 groups on each visit would be statistically assessed using the 2-sample *t* test or the Mann–Whitney test, depending on whether the normality is satisfied. For missing values, a last observation carried forward method would be used to handle.

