### 2.2. Sample size and recruitment

The exact calculation of the number of participants for statistical analysis for this pilot study is challenging because owing to the few reports on BMA. The number of participants for a pilot study should be at least twelve people per group as suggested by a previous study.^[16]^ Considering a dropout rate of 20% owing to a total of 12 treatments for 4 weeks, this study requires fifteen participants per group. Thus, the total required participant number for this study is thirty.

Participants would be recruited via advertisements in a single hospital. If a patient desires to participate, investigators would detail the study. Then, the participant who voluntarily submits the written consent would be screened using the inclusion and exclusion criteria. If considered suitable, the participant would receive a unique participant number.

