### 2.3. Participants

#### 2.3.1.
*Inclusion criteria*.

Participants should satisfy all the following criteria:

Male and female aged between 19 and 65 years.Patients with dry eye having typical symptoms, including pruritus, foreign body sensation, irritation, pain, dryness, blurry eye, dazzle, eye congestion, and excessive lacrimation, and whose OSDI score is more than 13.Less than 10 mm/5 min in the Schirmer I test.Those who voluntarily submit the written consent.

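### The groups are compared on raw values at each visit without using visit 1 OSDI; this is valid on average but gives up precision that an ANCOVA could recover at almost no cost

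*Protocol article*

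**What the plan says.** Section 2.10.1 fixes a single approach: "The same analysis method will be used for the primary and secondary outcomes". It has two parts.

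- **Within groups:** "In the intragroup comparisons, the differences in the outcomes following the interventions would be analyzed using the" paired t test or the Wilcoxon signed-rank test, with 95% confidence intervals. Baseline is used only here.
- **Between groups:** the sentence opens "The differences between the 2 groups on each visit would be statistically assessed using the 2-sample" and goes on to name the t test, with Mann–Whitney as the alternative. Which of them applies is decided "depending on whether the normality is satisfied". No covariate or change score is named, and no confidence interval is mentioned in this sentence.

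Section 2.9.1 names the outcome ("The primary outcome of this study is OSDI") and its timing: "The OSDI is assessed on visit 1 (prior to intervention), 7, and 13". A baseline value is therefore scheduled for every participant. Read literally, testing at each visit also includes a significance test between the groups at visit 1.

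**The concern.** The trial aims to show superiority of BMA over IDA (section 1), and its results are meant to support a larger trial (section 3). Both uses rest on the between-group difference, which 30 patients estimate poorly.

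Baseline severity may vary widely. Entry asks only for a patient "whose OSDI score is more than 13" on a 0–100 scale (section 2.3.1), which admits mild to severe disease. Section 2.4 describes blocks of 4 and mentions no stratification by OSDI. A test on raw final values leaves the part of the spread that baseline predicts in the error term. In any one randomization it also carries a chance baseline difference through to the result.

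Separately, making the test depend on a normality check leaves the primary method open until the data are in. The t test and the Mann–Whitney test do not address the same hypothesis, and the choice could differ between visits 7 and 13.

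**Working it through.** **The plan's own figure.** Section 2.2 starts from a rule of thumb: "The number of participants for a pilot study should be at least twelve people per group". With 20% dropout, 12 / (1 - 0.20) = 15 per group, 30 in total. This reproduces. The article gives no alpha, power, effect size or SD, so there is no stated power figure to check.

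**Assumptions.** Two-sided alpha 0.05, normal outcomes, equal variances and a common slope. The correlation r between visit 1 and visit 13 OSDI is not in the documents, so a range from 0 to 0.7 is shown.

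**Step 1: chance imbalance at baseline.** The SE of the baseline difference in SD units is sqrt(2/n).

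- n = 15: sqrt(2/15) = 0.365. P(|difference| > 0.5 SD) = 2[1 - Φ(0.5/0.365)] = 17%.
- n = 12: sqrt(2/12) = 0.408. The same probability is 22%.

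**Step 2: effect on the raw result.** A baseline difference of 0.5 SD shifts the expected raw visit 13 difference by 0.5 × r SD: 0.15, 0.25 and 0.35 SD at r = 0.3, 0.5 and 0.7.

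**Step 3: variance under ANCOVA relative to the raw comparison.** The ratio is (1 - r²) × (1 + 1/(2n - 4)). The second factor is the price of estimating the slope. At n = 15 it is 1 + 1/26 = 1.038. Detectable differences come from the noncentral t with 28 df (raw) and 27 df (ANCOVA).

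| r | Variance ratio, n = 15 | Change | Detectable difference, 80% power | Power at an assumed 0.8 SD |
|---|---|---|---|---|
| raw test | 1 | – | 1.06 SD | 56% |
| 0 | 1.038 | +4% | 1.08 SD | 55% |
| 0.2 | 0.96 × 1.038 = 0.997 | 0% | 1.06 SD | 56% |
| 0.3 | 0.91 × 1.038 = 0.945 | -5% | 1.03 SD | 58% |
| 0.5 | 0.75 × 1.038 = 0.779 | -22% | 0.94 SD | 67% |
| 0.7 | 0.51 × 1.038 = 0.530 | -47% | 0.77 SD | 83% |

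In patient terms, 15 per arm then does the work of 15/0.779 = 19 per arm at r = 0.5 and 15/0.530 = 28 at r = 0.7, but only 15/0.945 = 16 at r = 0.3. With 12 per arm, power at 0.8 SD is 47% for the raw test and 48%, 56% and 72% for ANCOVA at r = 0.3, 0.5 and 0.7.

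**Step 4: validity.** In 20,000 simulated trials per setting with no true difference and n = 15, the raw t test rejected in 4.9–5.1% and ANCOVA in 4.7–4.9%.

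**Step 5: change scores are not the remedy.** Their variance relative to the raw comparison is 2(1 - r), which is 1.4 at r = 0.3, 1.0 at 0.5 and 0.6 at 0.7. They are worse than the raw test below r = 0.5.

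**Step 6: the normality rule.** Shapiro–Wilk in each arm at 5% was assumed, since the article names no test. Simulated type I error of the two-stage procedure at 12–15 per arm was about 5.1–5.2% for normal data and 5.5–5.6% for skewed gamma data. With normal data, n = 15 and a true difference of 1 SD, the two tests disagree on significance in about 6–7% of datasets. Under the null they disagree in about 2%. The rule selects Mann–Whitney in only about 10% of normal datasets.

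**The case against.** The strongest reply is that nothing here is invalid. Under randomization the raw comparison is unbiased, and its standard error already allows for chance imbalance. The 17% and 22% are chances of an uneven start and do not give the chance of a wrong conclusion. This stands: a reader might infer that the primary test is biased or has inflated error, and Step 4 shows otherwise.

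The gain depends on a correlation that the article does not give and that the OSDI entry cut-off may lower. At about 0.2 there is nothing to gain, and at zero there is a small loss. This also stands, and it is why the full range is shown.

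A reader might take the normality-dependent choice as serious data-driven selection. The rule is set in advance and depends on distribution shape, not on which p-value is smaller. Step 6 shows little harm to type I error. Naming one method is tidier, but this is a secondary matter.

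A reader might also suspect that visit 1 OSDI is collected after the envelope is opened in front of an unblinded participant. The documents do not support that. Section 2.8.2 lists the visit 1 measurements before it mentions allocation, and Table 2 schedules OSDI and Schirmer I at screening as well, with allocation after screening (section 2.4).

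Finally, this is a pilot sized by a rule of thumb, section 3 concedes that it is small, and a separate analysis plan might specify adjustment. No stated power is contradicted. The point still holds because the article names a between-group method and that method ignores baseline.

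**Conclusion.** The point holds as one of efficiency. The stated between-group analysis leaves out a baseline measurement that every participant is scheduled to have, in a trial with few patients to spare. At 15 per arm, ANCOVA would cut the variance by roughly a fifth at r = 0.5 and by nearly half at r = 0.7. The gain is small at 0.3 and absent at 0.2 or below. These figures rest on an assumed r and on approximate normality. They describe precision and how far a single unlucky randomization could move the result. They do not show bias on average, inflated type I error or a shortfall against any stated target. The change is worth making because the possible gain is large compared with the worst case, about 4% more variance.

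**What to change.** Before outcome data are examined by arm, record the following in the analysis plan or an amendment:

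- **Primary comparison:** ANCOVA of visit 13 OSDI on arm with visit 1 OSDI as covariate, reported as the adjusted mean difference with its 95% CI. This is the single primary method and replaces the normality-dependent choice.
- **VAS and Schirmer I:** the same model, each with its own visit 1 value as covariate.
- **Rank-based test:** one named test as a sensitivity analysis for OSDI, and as the analysis of the 0–6 QoL item, for which a linear model is harder to justify.
- **Visit 1:** descriptive statistics only, with no significance test between groups.

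**Cost.** Wording only: no extra visit, measurement or patient, and no change to trial conduct. The analysis spends one degree of freedom and loses slightly if r is near zero. Reporting the observed r would also help to size the planned larger trial.
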